### Participants

The research team worked in public health nursing, home care nursing, public health, statistics, and computer sciences. This study is divided 2 phases. In phase 1, the research team conducted a literature review and a panel discussion that included 3 supervisors with experience working as prefectural or municipal government PHNs and 1 executive director of the Japan Nurse Association. The criteria for convening the expert panels meeting were to gather their opinions on the draft architectural framework—a hypothetical algorithm to determine the need for practice review; moreover, each item was developed by the research team.

In phase 2, the participants of interviews will be supervisory PHNs in prefectures or municipalities. Additionally, to ensure nationwide representation, we will include supervisory PHNs and midcareer PHNs with experience working in all local governments in Japan except those that completed the interviews. The inclusion criteria of midcareer PHNs have their cases and experience working for 6 to 20 years. The exclusion criteria for them are a managerial position.

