### Recruitment

In phase 1, the research team recruited a panel of experts using snowball sampling. In phase 2, they recruited 5 to 10 supervisory PHNs as participants, who worked in prefectures or municipalities to avoid bias in the functions and roles of public health centers. Before starting the nationwide survey, we sent letters, including the study description, to supervisory PHNs. We used a mailing list of all supervisory PHNs from the Ministry of Health, Labour and Welfare to announce the survey by email. We expect approximately 530 local governments to participate based on a collection rate of 30% in a previous study that used a similar survey methodology [29].

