### Data Analysis

In the qualitative phase, 3 researchers will read the interview transcripts (confirmed by the interviewees) and classify the contents in terms of the survey items using the content analysis method [33]. We will combine expressions with similar meanings into a single concept, whereas contradictory data will be left as is. After consulting with the project’s supervisory PHNs, we will revise the survey items. The items for the nationwide survey will be finalized after all the project members confirm their validity.

The nationwide survey will be conducted through a descriptive analysis of the components of the system and the subjective necessity of PHN practices. In this survey, PHNs will answer based on 2 types of activities: (1) highly unnecessary and (2) highly essential. We want to compare these 2 categories and confirm whether the items will effectively work to help identify the differences between each activity in terms of necessity. We will use Cronbach α to measure the degree of agreement between the importance calculated when the responses were applied to the system developed in phase 1 and the subjective importance expressed by PHN interviewees. We will also perform a decision tree or random forest analysis with the PHN’s subjective sense of significance as the outcome and the system configuration items as explanatory variables. The model with the highest prediction accuracy will be compared with the system created in phase 1. Finally, the panels will verify the nationwide survey results to confirm the external validity and consider whether the system may be improved based on the findings.

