### Items From a Cloud-Based Practice Record System

In phase 1, the panels agreed that the draft architectural framework and a hypothetical algorithm were reasonable. After meetings with them, we decided that the system should not be linked to electronic nursing records to protect the privacy of each individual case. Items from a cloud-based practice record system are depicted in Tables 1 and 2. The items were divided into 2 domains. The first was a daily record system regarding individual care, community activities, and developing needs-oriented projects, whereas the second was their termly review system. Based on the Omaha system framework [14], we added assessment items from the perspectives of the individual, the family, and the environment, especially for individual care. We used 9 categories regarding a national survey of public health nursing activities [27]: infectious disease, intractable disease, disability, mental health, maternal and child health, health promotion, aging and long-term care, occupational health, and child welfare.

After developing the parts of the system, the researchers entered the data using typical vignette cases based on the national examination level and modified the items based on the results. The expert panels also filled in the items. However, the vignette cases were more straightforward than the actual clients. Therefore, we will ask PHNs to answer each item in the nationwide survey based on their actual cases (see below for more information).

**Table 1 table1:** Items from a cloud-based practice record system: individual care.

System, unit, category/domain, and examples of items							Items, n

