Moreover, because the system requires PHNs to record their daily activities, it will enable PHN directors and staff to reflect on their practice periodically. Sharing the results of their daily activities with tier supervisors can help PHNs improve their performance and provide appropriate care for individuals, families, aggregates, and communities. Therefore, this study will improve the quality of care and address community health inequities.

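### External validity is to be confirmed by a panel's review of the survey results, a step that can support only face or content validity

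*Protocol article*

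**What the plan says.** After the survey analyses, the Data Analysis section adds a last step: "the panels will verify the nationwide survey results to confirm the external validity". In the same step the panels consider whether the findings suggest improvements to the system.

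The Participants section describes the phase 1 panel as "a panel discussion that included 3 supervisors with experience working as prefectural or municipal government PHNs and 1 executive director". On how it was formed, the Recruitment section says that "the research team recruited a panel of experts using snowball sampling". The Results section on the system's items reports the panel's part in development: "In phase 1, the panels agreed that the draft architectural framework and a hypothetical algorithm were reasonable", and "After meetings with them, we decided that the system should not be linked to electronic nursing records". It adds that the panel also completed the items.

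The survey asks PHNs to enter real activities from the past month and to rate the necessity of each from 1 to 10. The Data Analysis section compares the importance calculated by the phase 1 system with the PHNs' own rating. It also fits a decision tree or random forest to that subjective rating. The Objective nevertheless includes determining best practices, and the Discussion concludes: "Therefore, this study will improve the quality of care and address community health inequities".

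**The concern.** External validity is a statement about performance: does the tool work in people and settings that played no part in building it? A panel can say whether results look plausible or whether items cover the right ground. It cannot observe performance elsewhere. A panel that helped shape the tool is also poorly placed to give an independent opinion.

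At stake is the label on the finished system. A report could say that external validity was confirmed, and that best practices were determined, when the external validity statement rests on expert opinion and the best-practice statement has no care or health outcome behind it. The article expects supervisors to use the system to benchmark staff and departments, so users would rely on that label.

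**Working it through.** The article states no sample size, power or threshold for this step, so there is no figure to reproduce. The check sets the sections side by side.

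**1. Which panel.** The Abstract and the Participants section give 3 supervisors + 1 executive director = 4 people, taking that list as complete. No other panel is defined, and the term is used throughout for this group. That it is also the phase 2 panel is therefore an inference, though a strong one.

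**2. Its independence.** Members were found by snowball sampling through the research team. Before the survey they had endorsed the framework and algorithm, met with the team before a design decision was made, and completed the items.

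**3. What each source of evidence can support.**

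| Source | New to the phase 1 algorithm? | What it can support |
|---|---|---|
| Vignettes and panel completion of items (phase 1) | No, used to develop the items | Content, feasibility |
| Survey cases scored by the phase 1 system | Yes | Agreement with PHN ratings in new settings |
| Tree or random forest fitted to survey cases | No for the fitted model, unless cases are held out | External performance only in held-out governments |
| Panel review of survey results | Not a data source | Face or content validity, interpretation |

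The second row is the one that bears on external validity for the phase 1 system. The Participants section also excludes the interviewed governments from the survey. The plan nevertheless attaches the claim to the last row.

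**4. Criterion against claim.** The reference in the survey analyses is the PHN's subjective rating. Table 2 has items on disparity and on whether the initial health issue was resolved, but PHNs complete these as inputs to the system. No described analysis uses a care or health outcome as the criterion. Agreement with perceived necessity is the most that can be shown.

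**5. Context on size.**
- The Recruitment section expects about 530 governments at a 30% collection rate, so the implied base is 530 / 0.30 ≈ 1,767. The article does not state this base.
- The Abstract reports 177 governments for supervisory PHNs: 177 / 1,767 = 10.0%, and 177 / 530 = 33% of the expected number.
- It reports 196 for midcareer PHNs: 196 / 1,767 = 11.1%, and 196 / 530 = 37%. This assumes that both counts are governments on the same base.
- Suppose, generously, that the four panel members were a random sample and all agreed. The exact 95% lower limit for agreement among such experts would be 0.025^(1/4) = 0.40. They are not a random sample, and agreement among experts is not performance.

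**The case against.** The strongest reply is that the study does have external data. The algorithm came from a literature review, team meetings, vignettes and panel input, and the survey then brings in real cases from practising PHNs. This stands. A reader might infer that the plan has no independent cases at all, but the Procedures and Data Analysis sections contradict that reading. The fault lies in which step is credited with external validity.

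A reader might also infer that the panel step itself revises the system and that a revised version will be presented as validated. The text says only that improvement will be considered, and nowhere assigns a validity label to a later version. What remains is narrower: no later data collection is described, so a version changed at that point would have no validation data in this study.

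Three further replies have some force:
- The panel members are listed separately from the research team, so they are not the developers. Their part in development still limits their independence.
- A condensed article may leave the review procedure, and the resampling for the models, to the full protocol. That is fair, but no procedure for collecting opinion would turn it into evidence of performance elsewhere.
- The sentence on the panel does not mention best practice, and the Limitations section admits selection bias. The best-practice claim comes from the Objective and Conclusions, and the admitted limitation does not cover the lack of an outcome criterion.

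Nor does the article show that the survey is large enough for validation by region. It gives no split by region or government type, and item sets differ by activity domain, so groups may be thin.

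**Conclusion.** The point holds in a limited form. The plan assigns confirmation of external validity to a review by what is, on the natural reading, the four-person phase 1 panel. That review can support face or content validity only. Usable evidence on external performance exists in the survey, in the phase 1 system's agreement with PHN ratings of new cases, and the claim should rest there. Because perceived necessity is the only criterion, the design cannot determine best practices or show improved care.

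The collected data are not invalidated. What changes is the property the study may claim and the reach of its conclusion. Response at roughly 10% to 11% of the implied base, if that base applies, makes generalisation more fragile, and panel endorsement cannot repair it.

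**What to change.** 1. Describe the panel step as expert review for face or content validity and for interpretation.
2. Base any statement on external validity on the phase 1 system's performance in the survey cases. For the tree or random forest, report performance in local governments held out whole, for example leaving out one region at a time, or prefectures against municipalities, where group sizes allow. Report the spread across groups as well as the average.
3. Name the version that was tested. The items were to be revised after the interviews and before the survey, so say which items and which scoring rule the results refer to. State that any version changed after the panel review is not yet validated.
4. Limit the conclusions to agreement with PHN-perceived necessity. Do not claim to have determined best practices or improved care.

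The cost is wording changes and one rerun of the models on data already collected. Estimates in small groups may be imprecise, and the stated conclusion will be more modest.

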### Ethical Considerations

This study will be conducted following the Declaration of Helsinki. Ethical approval for this study was obtained from the Research Ethics Committee of the Faculty of Medicine of the University of Tokyo, review number ID=2022114NI, 2022114NI-(1), 2022114NI-(2). We will explain the study’s purpose and methods to the interviewees and advise them that their privacy will be protected in written form. Informed consent will be obtained from each participant. For the nationwide survey, only those who agree to participate in the study will be asked to respond to the questionnaire.

## Results

### Overview

This study was supported by the Ministry of Health, Labour and Welfare Japan research grant, which was acquired in April 2022. Interviews for supervisory PHNs were started in September 2022. Additionally, participants in the nationwide survey will be recruited in December 2022. The estimated date of the nationwide survey’s completion will be January 2023. The preliminary results will be submitted for publication in December 2023.

### Items From a Cloud-Based Practice Record System

In phase 1, the panels agreed that the draft architectural framework and a hypothetical algorithm were reasonable. After meetings with them, we decided that the system should not be linked to electronic nursing records to protect the privacy of each individual case. Items from a cloud-based practice record system are depicted in Tables 1 and 2. The items were divided into 2 domains. The first was a daily record system regarding individual care, community activities, and developing needs-oriented projects, whereas the second was their termly review system. Based on the Omaha system framework [14], we added assessment items from the perspectives of the individual, the family, and the environment, especially for individual care. We used 9 categories regarding a national survey of public health nursing activities [27]: infectious disease, intractable disease, disability, mental health, maternal and child health, health promotion, aging and long-term care, occupational health, and child welfare.

After developing the parts of the system, the researchers entered the data using typical vignette cases based on the national examination level and modified the items based on the results. The expert panels also filled in the items. However, the vignette cases were more straightforward than the actual clients. Therefore, we will ask PHNs to answer each item in the nationwide survey based on their actual cases (see below for more information).

**Table 1 table1:** Items from a cloud-based practice record system: individual care.

System, unit, category/domain, and examples of items							Items, n
**Daily record system (N=71-89^a^)**							
	**Transdomain items (n=69)**						
		**Demographics of the PHNs^b^**				5	
			PHN ID				
			Dates				
			Districts				
			Activity domains				
			Time consumed				
		**Necessity**				44	
			**Individual**				
				Symptom: acute deterioration of medical condition			
				ADL^c^: dependent in basic ADLs			
				Acceptance: refusal of support, consultation, or treatment			
				Treatment: need medical care at home			
				Communication: difficulty in communication			
				Social support: absence of key persons			
				Emergency: risk of self-injury			
			**Family**				
				Symptom: family member’s poor health			
				Acceptance: family member’s refusal of support, consultation, or treatment			
				Communication: family member’s lack of problem awareness and coping skills			
				Social support: family member’s absence of someone to consult			
				Emergency: domestic violence			
			**Environment**				
				Housing: unsanitary living environment			
				Social resource: lack of social resources available			
				Economic: economic deprivation (insufficient income)			
				Neighborhood: trouble with neighbors			
		Daily review: the problem is worsening or is expected to worsen				9	
		Activity selection: cooperation of community residents is necessary to solve the problem				6	
		Task load: how irritated, stressed, and annoyed did you feel during the task?				5	
	**Domain-specific items (N=2-20^a^)**						
		**Necessity**					
			Infectious disease: risk of outbreak		10		
			Intractable disease: support immediately after diagnosis or discharge		5		
			Disability: problems in employment or social participation		5		
			Mental health: disturbance of life rhythm		2		
			Maternal and child health: caregiver’s risk in life history (eg, history of childhood abuse)		5		
			Health promotion: refusal of specific health guidance		7		
			Aging and long-term care: behavioral and psychological symptoms of dementia		4		
			Occupational health: young caregiver		20		
**Termly review system (N=14)**							
	Termly review: imbalance in the number and load of cases per PHN/district					4	
	Activity selection: accumulation of cases with similar needs					10	

^a^Number of items depends on the domain.

^b^PHN: public health nurse.

^c^ADL: activities of daily living.

**Table 2 table2:** Items from a cloud-based practice record system: community-based activities and project development.

Unit, category/domain, and example of items							Items, n
**Daily record system (N=26)**							
	**Demographics of the PHNs^a^**						5
			PHNs ID				
			Dates				
			Districts				
			Activity domains				
			Time consumed				
	Necessity: risk to the life and well-being of the participants						4
	Daily review: fewer participants in the activity/project than expected						3
	Activity selection: people who have interrupted their participation and need individual follow-up						2
	Task load: decreased involvement of residents in the operation of activity/project						12
**Termly review system (N=57)**							
	Necessity: data available that support the necessity						12
	**Termly review**						
		Prediction and evaluation: initial health issue resolved and low probability of relapse				10	
		Disparity: inequity in service provision between regions or target groups				3	
		Substitutability: alternative private services available				5	
		Institutional issue: end of the year as a subsidized project				2	
		Resource: lack of cooperation with key persons in the district				8	
		Aggregated: long-term and large number of PHN inputs determined the project is less necessary				3	
	**Activity selection**						
		Community-based activities to project development: enactment or amendment of laws related to activities/project			10		
		Project to community-based activities: necessity to modify the operation of the project depending on the district			4		

^a^PHN: Public health nurse.

#### Daily Record System

The daily record system has 5 units: (1) demographic information of PHNs, (2) assessment of the necessity, (3) daily review, (4) activity selection, and (5) task load [34]. PHNs will enter related data daily, as described below.

Demographics of the PHN unit. PHNs will input their IDs, dates of their activities, districts, activity domains, and the time required for each activity.Assessment of the necessity unit. The “necessity unit” determines how necessary each PHN activity is. The necessity of an individual case is determined by checking an applicable option (applicable, not applicable, or unknown) for each of the necessity judgment items in the domain to which each case corresponds to determine clinical urgency and any problems. The level of necessity of community-based activities and project development practices will be determined by checking the transdomain items and recording the number of people—the activity and practice targets.Daily review unit. It evaluates PHN activities to determine whether they are appropriate and worth continuing. Items are distributed across the individual care, community-based activity, and project development subsets.Activity selection unit. It examines movements across the different types of PHN activities. Individual care practices include items that speak to or can develop into community-based activities and project development practices.Task load unit. It determines the difficulty level of each activity. Individual care difficulty will be measured using the Japanese version of the National Aeronautics and Space Administration task load index. This considers mental, physical, and temporal demands, level of effort, performance, and frustration [34].

#### Termly Review System

The termly review system assesses each activity by collecting monthly or semiannual daily reports and inputting additional items, including (1) necessity, (2) the termly review, and (3) activity selection units.

Necessity unit. It consists of items that determine the necessity of community-based activities and project development from a long-term perspective. The term review unit in individual care activities is automatically checked based on accumulated daily reports.Termly review unit. The termly review items for community-based activities and project development will be itemized regarding forecasting and evaluation, gaps, substitutability, institutions, and limitations.Activity selection unit. The activity selection unit in the termly reviewed system determines guidelines for the future activities of each PHN. The individual care subsection includes accumulated daily reports and additional items that choose complexity, multiproblematic cases, and rapid changes in social needs. Meanwhile, the community-based activities and project development subsections comprise automatic checks based on accumulated daily reports and items involved in transitions between activity types, such as health crises or government policy changes.

